## **5.0 Ethical Considerations**

This project will be conducted in accordance with the Research Ethics Boards of SFU, UBC and the Tri-Council Policy Statement on Research Involving Human Subjects. The research team at CARMHA has extensive experience managing large databases of sensitive information. No identifying personal information about the study participants will be kept with any of the interview or administrative data. All electronic and paper records will be maintained using existing protocols and facilities at SFU Harbour Centre. Dedicated server rooms, work stations, and filing systems are all maintained in a secure environment that is audited for security and compliance with best practice. Records linking participants' study identification number and personal data will be kept under lock by the Research Coordinator at CARMHA, in a location separate from where questionnaires will be stored. Identifiers will be removed from all data as soon as possible. Furthermore, all research personnel who have access to raw data will be bound by confidentiality agreements.

### **5.1 Quantitative Data**

**Risks to subjects.** *Human subjects involvement.* Baseline interviews will be conducted with 500 participants with four follow-up interviews over a period of 2 years. All participants will be of legal adult status. Potential risks associated with the interviews are embarrassment and discomfort from discussing matters such as personal mental health problems or drug use. However, past research with similar surveys indicates that such risk is minimal. Further, these potential risks can be minimized by training interviewers carefully and by assuring subjects that interviews will be conducted in private. Another potential risk involves updating contact information at each follow-up interview with respondents who had nearly been lost to follow-up. This information is given voluntarily, and respondents will be familiarized with this process.

Within the context of this study, it is expected that the mental health problems and symptoms of both the moderate and high needs groups will diminish over time. Given the target population and the chronic nature of mental illness, it is likely that some individuals will, over time, move between the high and moderate needs group. However, there is a possibility that some individuals in the moderate need group could experience a significant escalation in their symptoms. In this event, the individual's case will be brought forward to an as yet to be determined committee of researchers and service providers, including a physician, in order to evaluate whether or not the individual or others are in significant danger. In the event that the committee determines the individual is a risk to self or others, the individual will be referred for more intensive treatment.

Physical health examinations (PHE) will be completed with a subset (20%) of study participants at baseline and at 24 months following baseline. PHEs will be carried out by qualified physicians who have expertise providing care to homeless and seriously ill urban patients. Participants will have the option of refusing or discontinuing PHEs at any point. The PHE are anticipated to reveal untreated or undertreated health conditions, which may require immediate or urgent treatment. Good clinical practice will govern the follow up and treatment of medical conditions identified in PHEs.

**Adequacy of Protection Against Risks.** *Informed Consent.* Prior to the baseline interview, all respondents will be evaluated for competency with regard to their ability to understand informed consent. Once competency has been established, signed informed consent will be obtained from all respondents. A lengthy consent form will be read to the respondent authorizing consent to be interviewed, to be randomized to a housing and services group, to have administrative records accessed by the study team, to participate in the qualitative interviews, and to be re-contacted for the follow-up or longitudinal tracing through personal contact information and through public records. As part of the informed consent process, individuals will be informed that: (a) participation is voluntary, and that there are no consequences for refusal to participate; (b) they could be randomized to a condition of 'usual care'; (c) participation will involve answering questions about their background, health problems, housing circumstances, and their experiences with services; (d) even after consenting to participate, participants can interrupt the interview at any point or refuse any treatment, services or to answer any question; (e) all responses and results will be entirely confidential, and no identifying information will appear in any material associated with the study; and (f) no information about respondents as individuals will be shared with parties outside the research team. At each subsequent follow-up interview, verbal consent will be obtained after providing study participants with a description of the general content of the interview, notifying them that all information will remain completely confidential, and that participating in the study will be completely voluntary. After the interview, information relevant to tracing and the next follow-up will be obtained. Respondents will receive a \$40 honorarium for their participation in each quantitative interview.

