#### 4.6.1 Physical and Mental Health

Mental health symptoms and severity (including substance use and all Axis I and II diagnoses) will be assessed using the Symptom Checklist (SCL-90) and the MINI or the Psychiatric Diagnostic Screening Questionnaire (PDSQ). Other instruments suggested for the assessment of substance dependence/abuse include the Global Appraisal of Individual Needs (GAINS) – Substance Problem Scale, the Diagnostic Interview Schedule (DIS) and the Opiate Treatment Index. Adverse events, stress, and trauma symptoms are additional variables of interest and could be measured using the START Outcome Scale, Childhood Trauma Questionnaire and/or Adverse Childhood Events Scale, and the Trauma Symptom Checklist-40.

Given the known high mortality and the dearth of data regarding physical health conditions among people who are homeless, 20% of participants (a random sample of 20 per group, for a total of 100) will be accompanied by peer researchers to a research office at St. Paul's Hospital where physical assessments will be coordinated. If participants are in treatment or have received a recent physical examination, we will ask the participant for permission to access relevant details from their health record. The specific assessments and timelines proposed for physical health examinations are summarized in Table 1. If a participant in any treatment group is identified as having a medical condition that is in need of treatment, appropriate referrals will be made. Participants will receive an honorarium of \$50 for each physical examination.

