| Research Team                                                           | 
 
Provides research guidance and expertise
 
                                                                                                                                                                                                                                                                                                           | 
 
PI & Co-PIs
 
Co-investigators
 
Site Coordinator
 
Research Coordinator
 
                                                                     | Bimonthly (more or less frequently if needed) |
| Sub-Research Teams (Physical Health; Psychosocial; Administrative Data) | 
 
Design, conduct and analyze research in respective areas
 
                                                                                                                                                                                                                                                                                           | Individual research teams (Project Manager/ Coordinator; research assistants, data analysts, etc.)                                                                                                                      | Weekly                                        |
| Advisory Committee                                                      | 
 
Provides strategic advice and
 
                                                                                                                                                                                                                                                                                                                      | 
 
People with Direct Experience
 
                                                                                                                                         | Quarterly                                     |

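### Consent promises, without exception, that nothing about an individual leaves the research team, yet the escalation step for moderate-need participants takes the case to a committee that includes service providers

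*Protocol*

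**What the plan says.** **The promise.** The informed-consent paragraph of Protocol Section 5.1 lists what each participant will be told. Item (e) is that "all responses and results will be entirely confidential". Item (f) is that "no information about respondents as individuals will be shared with parties outside the research team". At every later interview verbal consent is taken again, after "notifying them that all information will remain completely confidential". None of the three statements carries an exception.

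**The safeguard.** The risk paragraph of the same section deals with a moderate-need participant whose symptoms become significantly worse. There, "the individual's case will be brought forward to an as yet to be determined committee of researchers and service providers, including a physician". The committee judges whether the participant or anyone else is in danger. If it finds a risk, "the individual will be referred for more intensive treatment". The wording is mandatory and mentions no permission from the participant.

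**Who belongs to which body.** The table in Section 8.1 gives the Research Team as the principal and co-principal investigators, the co-investigators, the site coordinator and the research coordinator. The ACT, ICM, housing and congregate leads sit on a separate body, the Project Team.

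**The concern.** The Protocol fixes what participants are told and also fixes an action that departs from it. A consent form drafted faithfully from items (e) and (f) would misdescribe what the study will do if the escalation step is used. Staff who have to start that step would hold two incompatible instructions about sensitive mental-health information.

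At stake are the accuracy of the consent and a clear path for the safeguard. This is not a detail that the Protocol has merely left for a later document, because both rules are already written down.

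**Working it through.** No formula decides this point. The passages have to be set side by side.

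1. **Scope of the promise.** It covers all responses and results and all information about individuals, and its boundary is the research team. It is given at baseline and at four follow-ups. No section of the Protocol states a limit for danger to the participant or to others.
2. **What the safeguard does.** It places an identified person's case before a mixed group. Researchers on that group may be inside the boundary. Service providers are named as members in their own right.
3. **Are service providers inside the boundary?** Section 8.1 does not list them in the Research Team and puts the service leads elsewhere. Section 4.6.2.2 does allow service providers to conduct some interviews, so the boundary is not sharp. That does not bring the providers on this committee, or a service receiving a referral, inside the team.
4. **Is permission implied?** The Protocol writes a permission step where it intends one: for access to health records (Section 4.6.1) and before interviewing a participant's service providers (Section 4.6.2.2). The escalation paragraph has none. The authorisations listed in the consent paragraph cover the interview, randomization, administrative records, qualitative interviews and tracing. Disclosure for safety is not among them.
5. **Does the step draw on research information?** The Protocol does not name the source. An ICM case manager may see the worsening directly (Section 4.4.3). The moderate-need usual-care group has no study service team (Section 4.4.5), so the study's own contacts are the likeliest source there. This is an inference.

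**How many people the conflict covers.** Section 5.1 gives 500 participants. Section 4.6.1 samples 20 per group for a total of 100, so there are 100 / 20 = 5 groups. Section 4.0 gives the moderate-need trial two of them. With equal groups, 500 / 5 = 100 per group and 2 × 100 = 200 moderate-need participants. Equal size is an assumption. Section 4.3 says that the split by need will be tested empirically, and its footnote warns that moderate-need people may be under-sampled. The 200 are those to whom the step could apply. The Protocol gives no rate from which to project actual disclosures.

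**The case against.** The best case on the other side has four parts.

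- **The consent form is not shown.** It may state a limit on confidentiality. The Protocol also commits to the Tri-Council policy, to approval by both ethics boards before any contact, and to procedures still to be written. This lowers the severity. It does not remove the conflict, because a form with such a limit would depart from what the Protocol says participants are told.
- **The Section 8.1 table is a governance list.** Read strictly as the confidentiality boundary, it would exclude the research assistants and peer interviewers who must handle data. That is fair, and the table should not be called a definition. Even so, nothing in the Protocol places the committee's providers inside the team.
- **Permission could be sought when symptoms escalate.** It could, so it is too stark to say that either the consent is untrue or the safeguard is unusable. But the Protocol does not provide that route.
- **Referral need not breach the promise if the participant agrees.** This stands. The firm conflict is the committee's review of the case. The referral that follows is weaker support.

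A reader might also see a second contradiction in Section 4.6.1, where a participant "identified as having a medical condition that is in need of treatment, appropriate referrals will be made" after a physical examination. The text does not support that. Such a referral can be made with the participant's agreement. Section 4.6.1 asks permission before records are accessed, Section 5.1 lets participants refuse or stop examinations, and consent item (d) lets them refuse any treatment or service. Adding the 100 examined participants to the 200, less the 40 in both (2 × 20), to reach 260 affected people is therefore not justified.

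**Conclusion.** The conflict is real and narrow. An unqualified promise and a mandatory committee review stand in the same section and cannot both be carried out as written. The passages must be reconciled. The promise reaches all 500 participants. The conflict concerns the moderate-need group, about 200 on the equal-group assumption, at an unstated frequency.

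Severity is moderate. The point bears on the truth of the consent and the workability of a safeguard, and affects no outcome analysis. It rests on the Protocol's account of what participants are told, because the consent form itself is not available.

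Two further inferences are tempting but unsupported. One is an interviewer who hears a plan of harm and must choose between promise and safety; the stated trigger is worsening symptoms in the moderate-need group. The other is that the present wording causes refusal or under-reporting of harm, victimization or substance use; the Protocol gives no evidence of that. Whether the escalation rule itself is the right one is not judged here.

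**What to change.** - Amend consent items (e) and (f) and the follow-up verbal script. State that, if the escalation review in Section 5.1 is triggered, the minimum necessary information may be shared with that committee and, if it finds a risk to the participant or to others, with the service to which the person is referred.
- Cross-refer to that limit in the escalation paragraph.
- Bind committee members to confidentiality. Section 5.0 already requires agreements from research personnel with access to raw data.
- Optionally, clarify in Section 4.6.1 that referrals after physical examinations are made with the participant's agreement. No exception to confidentiality should be written for examination findings: it would permit disclosure of results, including infection screens, without permission.

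The change is to wording only and alters no clinical rule. Section 5.4 puts the ethics application after the grant award, so it can be made before submission. The small downside is that a stated limit may make some participants slightly less willing to disclose or enrol.

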## **5.2 Qualitative Data.**

**Human Subject Involvement.** The second component of this study includes in-depth interviews (one approximately 30 days following baseline study enrollment and the other approximately 18 months later) with 50 participants from the RCT. Respondents will be encouraged to address topics of interest using their own words. The baseline interview protocols, yet to be developed, will have an introductory discussion of the respondent's background and current situation. After establishing rapport, interviewers will turn to potentially more-sensitive topics, such as attitudes towards homelessness, substance abuse and interactions with service providers. Participants will receive an honorarium of \$50 for their participation.

**Potential risks.** This study component involves minimal risks to participants. Again, potential risks associated with the interview are embarrassment and discomfort in providing information about matters such as homelessness, mental health and drug use. However, the research team's past experience with similar populations indicates that such risk is minimal. Furthermore, these potential risks will be minimized through interviewer training and by assuring that the interviews will be conducted in private. Since we do not require respondents' names for this component of the study, we will seek a waiver of written informed consent and develop an oral informed-consent procedure.

**Adequacy of protection against risks.** *Informed consent and confidentiality.* All required components of informed consent will be included and reviewed with participants. To further minimize risks, we will maintain strict respondent confidentiality by conducting interviews in private locations, by employing an ID system to assure that respondent names are never associated with transcripts, by storing interview tapes and transcripts in secured locations and password-protecting computer files. Only select research staff will ever have access to identifying information.

### 5.3 Administrative Data.

**Risk to Subjects:** *Human Subject Involvement.* All study participants will be asked to provide consent for the researchers to utilize their personal identifiers (i.e., name, date of birth, personal health number) to obtain administrative data reflecting their health care utilization (hospital, physician services, prescriptions), social services utilization (income assistance, disability and unemployment benefits) and criminal justice encounters (arrests and Provincial sentences). Data will be sought retrospectively to 1996 and will be refreshed and updated each year through the active study period (2009-2013), and then bi-annually until 2019.

**Potential risks.** This study component involves minimal potential risks to participants. However, a potential risk associated with collection of the administrative data surrounds embarrassment and discomfort in the event that the individual's identity is compromised. In order to minimize this potential risk, the electronic dataset used for the analyses proposed here will include *no personal identifying information*. Results will be reported in ways that do not reveal respondent identities.

**Adequacy of protection against risks.** *Informed consent.* During the consent procedures we will emphasize that: a) participation is completely voluntary; b) even after consenting to participate, they may refuse access to their administrative data; c) and no personal identifying information will appear in any materials associated with the study. No identifying personal information about the study participants will be kept with any of the administrative data. Records linking participant's study identification number and administrative data will be kept under lock by the Project Manager at CARMHA. All personal identifiers will be removed from the administrative data as soon as possible.

### 5.4 Procedures for REB approval

Upon notice of grant award, an application for human subjects approval will be submitted to the Research Ethics Boards at SFU and UBC. The applications will be submitted simultaneously and will be identical with the exception of institutional requirements that vary. The application for ethics approval will include both the RCT studies as well as a request to utilize and publish the results drawn from the key informant interviews with persons with lived experience that were conducted under contract with the MHCC. Contact with human subjects will not proceed until REB approval has been obtained from both SFU and UBC.

### 6.0 Sustainability

We are committed to ensuring that all participants are able to maintain their housing and receive the supports required beyond this project. We have had initial discussions with BC Housing regarding the sustainability of housing subsidies for those in scattered-site units as well as possible transitional options for people housed in the congregate setting. It is possible that we will not be able to secure sufficient ongoing housing subsidies for all participants and transition to alternative housing and supports may be necessary. We will work with individuals and link to the BC Housing Coordinated Access to Housing team in Vancouver to ensure successful transitions as needed. It is anticipated that a significant number of the new housing units currently under development will be available both before and after the end of the project and we will explore these options with BC Housing as they become available. We will continue to forge a partnership with the Streethome Foundation and link to its work on housing and service reform locally. We have also held initial conversations with the BC Ministry of Health to explore ways to ensure sustainability of funding for the services required for participants post-project, particularly with respect to the ACT intervention. Through engagement of our advisory and oversight committees as well as through meetings with provincial and local decision makers, academics and service providers, and people with lived experience, we will create and sustain

momentum for the project. The local oversight committee, composed of senior decision-makers will also provide a mechanism to leverage funds both during and post-project. It will be critical to actively engage additional key stakeholders locally in order to successfully build a strong local environment for sustainability. In this regard, Vancouver Coastal Health Authority and Providence Health Care – which operates the hospital that provides the majority of emergency and acute hospital-based services to people who experience homelessness and mental illness – are key partners with whom we will need to build strong and formal partnerships both at a governance and operational level. Both organizations have been well represented throughout the Consortium development process. Now that we have identified service leads, it will be critical in the next month to work with both Vancouver Coastal Health Authority and Providence Health Care to clarify their respective roles in supporting implementation of all three of our identified interventions. Moving forward, we will actively explore evidence-based models such as networks/communities of practice to facilitate service integration and knowledge exchange within and between relevant partners and stakeholders.

